**5. Study Assessment**

**Screening and enrolment**

As part of the routine medical services provided at the health centre, all children with symptoms suggestive of malaria will be screened for malaria using a rapid diagnostic test. Positive tests are confirmed by microscopy. Children fulfilling inclusion criteria will be invited to participate in the study following informed consent.

**Follow up**

Children will be given a unique personal identification number and be given treatment after informed consent. The basic follow up schedule is shown below. Treatments, information to the children, clinical observations and adverse events will be recorded in the clinical record forms. The children will come to the health centre on days 0, 1, 2, 3, 7, 14, 21, 28, 35 and 42. If a child is not seen at the health centre he/she will be visited at home.

Table 3. Study outline

| Action | Study Day | | | | | | | | | |
| --- | --- | --- | --- | --- | --- | --- | --- | --- | --- | --- |
|  | 0 | 1 | 2 | 3 | 7 | 14 | 21 | 28 | 35 | 42 |
| Clinical Records Form 1 | + | + | + | + |  |  |  |  |  |  |
| Clinical Records Form 2 |  |  |  |  | + | + | + | + | + | + |
| Standard physical examination | + | + | + | + |  |  |  |  |  |  |
| Body weight | + |  |  |  |  |  |  |  |  |  |
| Thick and thin smear$ | + | + | + | + | + | + | + | + | + | + |
| Temperature | + | + | + | + | + | + | + | + | + | + |
| 100μL of blood on filter-paper for genotyping or drug analysis* | + |  |  |  | + | + | + | + | + | + |
| Haemoglobin level (Haemocue™) | + |  |  | + |  |  |  |  |  | + |
| Differential count (Haemocue™ WBC DIFF) | + |  |  | + | + | + | + |  |  |  |
| 200μL of blood for in vitro culturing# | + |  |  |  |  |  |  |  |  |  |

$ Twice daily on days 0, 1 and 2. *The volume of blood spotted on to filter-papers should be exactly 100μL. # from 50 children

**6. Data Management**

The principle investigator will ensure that the study protocol is strictly adhered to and that data are correctly collected and recorded on the case record form. Data will be entered into an EpiData database during the study.

**7. Sample size**

The PCR corrected day 42 ACPR of AL was 97% in 2008 ( = before the national recommendation was changed in favour of A). It is likely that DP should be as efficacious as AL and it is therefore appropriate to conduct a non-inferiority trial[13](#_ENREF_13). Assuming 97% ACPR for both treatments, 5% significance level (alpha), 80% power (1-beta) and a non-inferiority limit (d) of 5% 144 children are required in each arm. Assuming a 20% loss to follow up a total of 346 children should be included.

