**Block Randomization**

Identical slips of paper specifying treatment arm AL or DP will be put into an envelope. Each envelope will contain 20 slips from each group and children will randomly select one slip.

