**Analysis of data**

The data will be analysed using survival estimates of per protocol treatment failure rates but also intention to treat treatment failure rates. Final analysis will include a description of included children, proportions of adverse events and any serious adverse events, the proportion of children withdrawn or lost to follow up, the cumulative PCR corrected and uncorrected success and failure rates on day 42 and the proportion of early, late clinical and late parasitological treatment failures.

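### Study A's 144 per arm comes from a normal approximation that is optimistic at 97% cure: an interval that holds about 5% error has roughly 70-75% power, not 80%

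*Protocol*

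**What the plan says.** Study A is described as an open-label, randomised non-inferiority trial (Protocol, Study A, Study design). Section 7, Sample size, gives its only power statement. It assumes 97% ACPR in both arms and a "5% significance level (alpha"), and continues: "80% power (1-beta) and a non-inferiority limit (d) of 5% 144 children are required in each arm". It adds 20% for loss to follow-up, for a total of 346. It does not say whether the 5% is one- or two-sided, and it names no formula or test.

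Allocation is equal: "Each envelope will contain 20 slips from each group and children will randomly select one slip" (Block Randomization). Analysis of data plans "survival estimates of per protocol treatment failure rates", with intention-to-treat rates as well, and reports cumulative PCR-corrected success and failure on day 42. It names no confidence interval or non-inferiority test. That choice may properly sit in a statistical analysis plan that is not at hand, and its absence is not the point here.

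**The concern.** A sample size statement links four figures: alpha, power, margin and n. At cure rates near 100% the normal approximation behind the usual formula becomes unreliable, because the estimated standard error depends on a handful of failures. A sample in which DP happens to show few failures gives both a favourable difference and a short interval, so a Wald-type test declares non-inferiority too readily. The formula's 80% power then comes partly from excess false-positive results.

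If the analysis uses a Wald-type interval, the chance of accepting a drug that is truly 5 points worse is somewhat above the stated 5%. If it uses an interval that holds 5%, the chance of failing to show non-inferiority for a truly equal drug is nearer 28% than 20% at 144 per arm. An inconclusive result would then be read against a power that the design does not have.

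**Working it through.** **Inputs**, all from Study A of the protocol: ACPR 97% in both arms, alpha 5%, power 80%, margin d = 0.05, 144 evaluable children per arm (7. Sample size), and 1:1 allocation (Block Randomization).

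**Reproducing 144.** The unpooled normal-approximation formula is

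n = (z_alpha + z_beta)² × [p1(1 − p1) + p2(1 − p2)] / d².

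- One-sided 5%: (1.6449 + 0.8416)² × (2 × 0.97 × 0.03) / 0.05² = 6.1827 × 0.0582 / 0.0025 = 143.9, so 144.
- One-sided 2.5%: 182.7, so 183.

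The protocol's figure therefore identifies its own alpha as one-sided 5%.

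**How many failures support the approximation.** 144 × 0.03 = 4.3 expected per arm.

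**Exact operating characteristics at 144 per arm.** All 145 × 145 pairs of outcomes from two independent binomials were enumerated and each test was applied at one-sided 5%. Power is the probability of declaring non-inferiority at 97% v 97%. Type I error is the same probability at DP 92% v AL 97%.

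| Method | Type I error | Power |
|---|---|---|
| Wald (unpooled) | 6.2% | 80.0% |
| Agresti-Caffo | 5.5% | 77.6% |
| Likelihood ratio | 5.5% | 76.5% |
| Newcombe, Farrington-Manning, Miettinen-Nurminen | 4.6% | 72.4% |
| Exact unconditional score | 4.4% | 72.3% |
| Wald with continuity correction | 3.6% | 70.3% |

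No method in the table gives at most 5% error together with 80% power. For true AL rates of 95% to 99% the Wald error runs from 5.7% to 7.2%, while the Farrington-Manning error stays between 4.2% and 5.0%.

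**Sensitivity to the evaluable number.** Exact power moves in a sawtooth because the counts are discrete. A 20% loss from 346 leaves 346 × 0.8 = 276.8, or about 138 per arm, so values below 144 are relevant too.

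| Evaluable per arm | Power of score-type interval |
|---|---|
| 138 | 69.0% (Farrington-Manning), 73.5% (Newcombe) |
| 144 | 72.4% (both) |
| 150 | 75.4% (Newcombe) |
| 160 | 77.5% (Newcombe) |
| 165 | 80.0% (Newcombe) |
| 170 | 79.3% (Newcombe) |
| 175 | 81.7% (Farrington-Manning) |

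Power stays above 80% from about 174 (Newcombe) or 175 (Farrington-Manning).

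**Survival version of the analysis.** With complete follow-up, a Kaplan-Meier difference with a plain Greenwood interval is the Wald case. With censoring, a simulation assumed 173 children per arm, 20% loss spread evenly over the day 7 to day 42 visits, and failures mostly on days 21 to 35. These loss and failure patterns are assumptions and are not in the protocol. The Greenwood interval had about 81% power with about 6% error. A Newcombe-type interval built on the survival estimates had about 75% power with just under 5% error.

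**The case against.** The strongest reply is that no figure in the sample size section is miscalculated. The 144 is what a widely used formula returns, all such formulas are approximate, and the interval method can be left to the statistical analysis plan. Most of this stands. A reader might infer an arithmetic error, and there is none. A reader might also infer that the trial will run at 6% error, but the protocol names no test, so that holds only if a Wald or plain Greenwood interval is used. The excess is then about 1 percentage point at the planning boundary. Deferring the method does not make the statement accurate, however. Of the methods checked, each misses either the 5% or the 80% at 144, so the later choice only settles which figure gives way.

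Second, 72.4% is one point on a sawtooth, and in the planned survival analysis children lost before day 42 still contribute. This also stands. It is why the power is better given as a range of roughly 70-75% than as a single figure. If almost no one were lost, 346 enrolled would mean 173 per arm and about 80% power. The sample size section, though, counts that surplus as expected loss.

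Third, a reader might take the unstated sidedness to mean two-sided 5% and conclude that the shortfall is much larger. The protocol does not support that: 144 follows only from one-sided 5%, and the two-sided reading would have required 183.

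**Conclusion.** The concern holds in a moderate form. The sample size is the right output of its formula, but the formula is optimistic at 97% cure, and the stated 5% error and 80% power are not delivered together at 144 per arm. With a Wald or plain Greenwood interval, power is 80% and type I error about 6% at 92% v 97%. With a Newcombe or Farrington-Manning interval, type I error is about 5% or less at that boundary, and power is about 72% at 144 and roughly 70-75% for evaluable numbers near it. Power reaches about 80% only near 165-175 per arm. The gap in power, some 5 to 10 points, matters more than the excess error of about 1 point.

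These figures assume a true ACPR of 97% in both arms, a 5-point margin, one-sided 5%, and binomial outcomes in the children evaluated. Allowing for censoring in the survival analysis leaves the shortfall at about 5 points under the loss pattern simulated. The finding does not show that the design is unsound or that more children must be enrolled.

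**What to change.** In Study A, section 7 (Sample size):

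- State that alpha is one-sided 5%.
- State that non-inferiority on the day 42 PCR-corrected difference will be judged with a score-type interval (Newcombe or Farrington-Manning, or the equivalent built on the survival estimates) and not with a Wald or plain Greenwood interval.
- Restate the power for about 144 evaluable children per arm as roughly 70-75%.

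The Analysis of data section, or the statistical analysis plan, should name the same interval. The cost is two or three sentences. No added enrolment is required. The downside is that the stated power becomes less favourable.

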**Analysis of data**

The data will be analysed using survival estimates of per protocol treatment failure rates but also intention to treat treatment failure rates. Final analysis will include a description of included children, proportions of adverse events and any serious adverse events, the proportion of children withdrawn or lost to follow up, the cumulative PCR corrected and uncorrected success and failure rates on day 42 and the proportion of early, late clinical and late parasitological treatment failures.

**Dissemination of results**

Results will be presented to the staff at the Bandim health centre and the ministry of Health and will be published in an international peer reviewed journal.

**8. Ethical considerations**

**Approval by the national ethical committee.**

The study has been approved by the ethical review board in Bissau, Guinea-Bissau (0021/CNES/INASA/2012). Molecular analyses in Sweden have been approved by the Stockholm regional review board (2011/832-32/2).

**Informed consent**

Children will only be included in the study if a parent or guardian gives informed consent. As the illiteracy rate is high, the consent request will be told by the study nurse using the local language Creole. Details about the trial including risks and benefits will be explained and any questions answered. The Clinical record forms will then be signed - if possible by the parent/guardian otherwise by the study nurse

**Confidentiality**

All information on the children will remain confidential and only shared by the study team.

**Health care services**

Recruitment is done at the Bandim health centre. All children not recruited will be treated according to standard practice. Study children will receive free health care throughout the follow up for any illness related to malaria regardless of treatment outcome. If children are found to have disease not related to malaria children will be referred for appropriate medical care.

**Inducement**

Health care and medications will be free during the study period but no other gifts or payments will be made.

**B. Effectiveness and safety of artemether + lumefantrine and dihydroartemisinin + piperaquine for the treatment of uncomplicated malaria in Guinea-Bissau**

**Objectives**

The primary objective is to measure the effectiveness and safety of AL and DP in children aged 6 months to 12 years suffering from uncomplicated *P. falciparum* malaria. Other objectives are as for the efficacy study except that haemoglobin will not be assessed on day 3 and neutropenia will not be assessed.

**Study design**

This study will be identical to the efficacy study with only minor differences as outlined below. Ethical considerations are the same in both studies.

**Timing and duration of the study**

The study will start when the efficacy study ends which will most probably be during spring 2014. The study will continue until a sufficient number of children are included. This is expected to take approximately 18 months.

**Treatment**

Randomisation and treatment allocation will be as for the efficacy study. Medication will be provided but there will not be observed intake and there will be no visit to the health centre on the afternoon of day 0 or on days 1, 2 or 3. Follow up, sampling and data collection will be identical from day 7 and onwards.

**Sample size**

The effectiveness of AL in our ongoing study appears to be approximately 80%. We expect the effectiveness of DP to be higher probably about 90%. Assuming a power (1-beta) of (80%) and a significance level of 5% we need 197 children in each study arm. Assuming a 20% loss to follow up a total of 474 children need to be included.

